### Other study parameters

Potential confounding parameters, such as opposite cortex fractures, demographic data, length, weight and BMI will be recorded. Adverse events like re-operations, including hardware removal, will also be recorded**.**

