### Statistics

All data will be analyzed according to an intention-to-treat principle, implying that all patients who are randomized will be included in the analyses, and that they will be analyzed according to the group to which they were allocated. For those patients who will be lost to follow-up or will be re-operated during follow-up, the last available measurement or the last measurement will be forwarded (Last Value Carried Forward technique).

A multivariable linear regression method will be used to analyze the impact of LCW versus CWO HTO on postoperative alignment, posterior tibial slope, patellar height, leg length, VAS, KOOS, walking distance and patients with adverse events at the one-year follow-up. A multivariable logistic regression method will be used for the dichotomous outcome measures. Gender, age and baseline values for HKA angle, VAS knee, KOOS, walking distance, medial osteoarthritis more than joint space loss alone, and concurrent OA of the lateral compartment will be considered as possible confounders and are included in the regression models only if they change the relationship between dependent variable and type of HTO by at least 10%. The SPSS program will be used for the statistical analyses and a p-value of 0.05 is considered statistically significant.

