## Discussion

Although HTO remains quite successful after 10 years, OA with associated symptoms will progress. Some patients may require total knee replacement (TKR) [15]. Success of TKR for knee OA is well-established, and about 85% of patients are satisfied with the surgical outcome [16], therefore when considering HTO in the early treatment of symptomatic medial compartmental OA subsequent TKA should not be compromised. A randomized clinical trial showed significantly more patellar descent and tibial slope increase after MOW compared to the LCW technique [17]. This may cause exposure and patellar eversion problems during knee replacement that may compromise precision and accuracy of TKR [18]. The advantage of MOW is preservation of bone stock with tensioning of the medial collateral ligament. This may result in a more conservative amount of bone removed during knee joint replacement, so joint line elevation by using a thicker-than-desired tibial component in balancing the ligaments is less likely. Furthermore, unlike LCW, the relative position of the medullary canal is not altered. This may facilitate tibial component placement with intramedullary guidance.

An operative complication that may result in an adverse effect is intraoperative fracturing of the opposite cortex. Avoidance of opposite cortex fracture can be difficult though, and is generally limited by the angular size of the wedge. Opposite cortical fracture occurs often during the LCW technique [15]. A fractured medial cortex in LCW may lead to progressive movement of the distal tibia into a varus position [19]. In case of the MOW, instability at the MOW site due to disruption of the lateral cortical hinge potentially results in displacement of the osteotomy and may contribute to recurrent varus deformity [20]. Newer angular stable plate systems with locking screws seem to avoid this problem. Loss of correction may lead to a suboptimal result [11,21,22]. Still, HTO is considered a very successful surgical procedure with low complication rates. For instance, non-union in HTO is very rare, especially in LCW, and delayed union is seen in about 3-4% [23,24].

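### Covariates enter each model only if they move the treatment estimate by 10%: a data-driven rule that modestly inflates type I error in the logistic model and often drops prognostic baseline values

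*Protocol article*

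**What the plan says.** The Statistics section of the protocol article names eight candidate covariates: "Gender, age and baseline values for HKA angle, VAS knee, KOOS, walking distance", and "medial osteoarthritis more than joint space loss alone, and concurrent OA of the lateral compartment". It treats them as possible confounders that "are included in the regression models only if they change the relationship between dependent variable and type of HTO by at least 10" per cent.

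The rule applies to both families of model. For continuous outcomes, "A multivariable linear regression method will be used to analyze the impact of LCW versus CWO HTO on postoperative alignment" and on the secondary measures; for the rest, "A multivariable logistic regression method will be used for the dichotomous outcome measures". The result is then read so that "a p-value of 0.05 is considered statistically significant". No covariate is fixed in advance. The text does not say whether the 10% is judged on the regression coefficient or on the odds ratio, or whether candidates are screened singly or stepwise.

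The section Other study parameters gives a different list under a similar label: "Potential confounding parameters, such as opposite cortex fractures, demographic data, length, weight and BMI will be recorded". On cortex fracture, the Discussion describes an intraoperative complication and states: "A fractured medial cortex in LCW may lead to progressive movement of the distal tibia into a varus position".

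**The concern.** Change-in-estimate screening is a tool for observational data, where an imbalanced covariate may signal systematic confounding. Here allocation is randomised 1:1 in blocks, so there is no systematic confounding to find. Three problems follow.

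- The adjustment set is chosen by inspecting the treatment estimate, but the p-value is read as if the model had been fixed beforehand.
- The threshold is relative to the estimate. When the effect is near zero, trivial shifts exceed 10% of it, so the rule is least stable under the null.
- The rule ignores prognostic strength. A baseline value that predicts outcome well but happens to be balanced is left out, although gaining precision from such variables is the main reason to adjust in a randomised trial.

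At stake are the error rate of the logistic analysis of 2–6° success, which carries the sample size, and some precision in the continuous outcomes.

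**Working it through.** **1. The plan's own figure.** Sample size calculation: 60% v 85%, α = 0.05 (taken as two-sided), power 80%. With p̄ = 0.725,

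n = [1.960·√(2·0.725·0.275) + 0.842·√(0.60·0.40 + 0.85·0.15)]² / 0.25² = (1.238 + 0.510)² / 0.0625 ≈ 49 per group.

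This agrees with the stated 50, and the covariate rule does not affect it. At 55 per arm the design expects 55·0.40 + 55·0.15 ≈ 30 failures. Arm plus eight covariates would then leave about 30/9 ≈ 3.4 failures per coefficient.

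**2. Simulation inputs.** From the document: eight candidates, the 10% rule, 1:1 allocation, 100 or 110 patients, 5% level. Assumed: independent standard-normal covariates, KOOS counted as one, two of the eight prognostic at the strengths shown (or none), and null success rates of 72.5% and 60%. The rule was run four ways: singly or forward, on the coefficient or the odds-ratio scale. Monte Carlo standard error is about 0.4 points at 100 patients (3000 runs) and 0.25 points at 110 (8000 runs).

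**3. Logistic model, no true effect (% rejected).**

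| Patients | Log odds ratios per SD | Unadjusted | Two fixed | All eight | 10% rule |
|---|---|---|---|---|---|
| 100 | none | 4.2 | 4.6 | 5.4 | 5.7–6.1 |
| 100 | 0.5, 0.3 | 4.3 | 4.6 | 5.3 | 5.6–5.9 |
| 100 | 1.0, 0.5 | 4.4 | 4.9 | 6.0 | 6.1–7.1 |
| 110 | none | 4.9 | 5.1 | 5.9 | 5.8–6.1 |
| 110 | 0.5, 0.3 | 4.6–5.1 | 4.9–5.2 | 5.6–5.8 | 5.7–6.8 |
| 110 | 1.0, 0.5 | 4.5–5.2 | 4.9–5.2 | 5.7–5.8 | 6.2–7.2 |

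Forcing in all eight involves no selection, so its excess over 5% is small-sample behaviour of the Wald test. The rule minus all eight runs from about −0.1 points (5.79 − 5.90, no prognostic candidates) to 1.5 points (7.17 − 5.69). Where candidates are prognostic it lies mostly between 0.5 and 1.5. A further setting with 50 per arm and three prognostic covariates (log odds ratio 0.5) gave 6.5–7.0% under the rule, 4.3–4.8% unadjusted, 4.7% with one fixed covariate and 5.3–5.9% with all eight.

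The unstated scale matters. With no prognostic candidate at all, single screening picks about 3 of the 8 on the coefficient scale but only 0.4 to 0.5 on the odds-ratio scale.

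**4. Linear model, no true effect.** The rule rejects in 3.8% to 5.9%: no consistent inflation.

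**5. Prognostic covariates left out when there is an effect.**

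- Logistic, 60% v 85%, 110 patients: the strongest covariate is omitted in 61–69% of trials at log odds ratio 0.5, and in 26–32% at 1.0.
- Linear, 50 per arm, effect 0.5 SD, baseline correlation r = 0.5: omitted about 40% of the time.

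**6. Linear power.** Noncentrality = d·√(n/2)/√(1 − r²), with d = 0.5 and n = 50, so d·√(n/2) = 2.5. Power ≈ Φ(noncentrality − 1.984).

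- Unadjusted: 2.5, giving 70%.
- Baseline fixed, r = 0.5: 2.5/0.866 = 2.89, giving 82% (simulated 80–81%). The rule, simulated: 78%. Loss about 3 points.
- Baseline fixed, r = 0.3: 2.5/0.954 = 2.62, giving 74% (simulated 73%). The rule, simulated: 71–72%. Loss 1 to 2 points.

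A second setting used 110 patients and an effect of 0.55 residual SD, with power 80% for two fixed covariates. The rule gave 76–77% with slopes 0.5 and 0.3 (r = 0.5/√1.34 = 0.43 for the stronger) and 72–73% with slopes 1.0 and 0.5 (r = 1/√2.25 = 0.67).

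**7. Cortex fracture, sections side by side.** Other study parameters labels it a potential confounder. The Discussion places it during the operation, says it is frequent with the closing wedge, and ties it to loss of correction. It therefore arises after allocation and may lie between technique and alignment. It is not among the eight candidates in Statistics.

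**The case against.** The candidate list and the threshold are stated in advance, so the analyst's discretion is bounded. The inflation is at most about 2 points over nominal, and part of it would arise in any model with eight covariates and some 30 failures. Postoperative alignment and nearly all secondary outcomes go to linear regression, where no inflation appears, and the main endpoint section puts the continuous deviation from 4° beside the dichotomous outcome. The rule also beats no adjustment in the linear model: 78% v about 69% power at r = 0.5. In the logistic model at 60% v 85% it rejects in 81–85% of trials, against 80–83% with two fixed covariates, so no power is lost there. Finally, r = 0.5 may be too high for alignment, because every wedge is planned to the same 4° target, which should weaken the link between preoperative and final HKA angle.

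Most of this stands and limits the size of the point. It does not rescue the rule. Discretion is not fully bounded while scale and order of screening are open. The higher logistic rejection rate under an effect comes from a test that also rejects too often under the null. Fixed covariates hold the nominal level and do at least as well in the linear models at the strengths examined.

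**Conclusion.** The point holds and should be fixed, but it does not threaten the trial. Logistic type I error is about 5.6% to 7.2%, of which selection itself accounts for roughly 0.5 to 1.5 points. In linear models the cost is about 3 points of power at r = 0.5 and 1 to 2 at r = 0.3, reaching 7 to 9 only with a much stronger covariate (r about 0.67). All these figures rest on assumed covariate strengths and independence, since the document gives neither.

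Three stronger readings are not supported.

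- A reader might infer that fixing the baseline value would raise power from 70% to 80%. That compares it with no adjustment, which is not what the protocol plans.
- A reader might blame the inflation on non-collapsibility of the odds ratio. Under the null the marginal and conditional odds ratios are both 1, so it cannot be the cause. It matters only when there is an effect, where the odds ratio can shift even for a balanced covariate.
- A reader might infer that the analysis will adjust for cortex fracture and so remove part of the technique's effect. Statistics does not plan this and the documents give no fracture rates by arm, so no effect size can be claimed. What remains is a misleading label.

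**What to change.** Delete the 10% rule and name a small set of covariates in advance, drawn from the baseline variables already listed:

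- baseline HKA angle for the alignment outcomes, continuous and dichotomous;
- the outcome's own baseline value for VAS, KOOS and walking distance;
- the preoperative value for tibial slope, patellar height and leg length only where it is measured, because the protocol states these at one year only.

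Report the unadjusted result alongside, and say beforehand which of the two is the main analysis. Adding surgeon is optional and not needed to resolve this point. In Other study parameters, state that opposite cortex fracture is an outcome reported by arm and not an adjustment covariate.

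The cost is wording, plus a slight loss of degrees of freedom if a chosen covariate proves not to be prognostic. The sample size does not change.

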## Discussion

Although HTO remains quite successful after 10 years, OA with associated symptoms will progress. Some patients may require total knee replacement (TKR) [15]. Success of TKR for knee OA is well-established, and about 85% of patients are satisfied with the surgical outcome [16], therefore when considering HTO in the early treatment of symptomatic medial compartmental OA subsequent TKA should not be compromised. A randomized clinical trial showed significantly more patellar descent and tibial slope increase after MOW compared to the LCW technique [17]. This may cause exposure and patellar eversion problems during knee replacement that may compromise precision and accuracy of TKR [18]. The advantage of MOW is preservation of bone stock with tensioning of the medial collateral ligament. This may result in a more conservative amount of bone removed during knee joint replacement, so joint line elevation by using a thicker-than-desired tibial component in balancing the ligaments is less likely. Furthermore, unlike LCW, the relative position of the medullary canal is not altered. This may facilitate tibial component placement with intramedullary guidance.

An operative complication that may result in an adverse effect is intraoperative fracturing of the opposite cortex. Avoidance of opposite cortex fracture can be difficult though, and is generally limited by the angular size of the wedge. Opposite cortical fracture occurs often during the LCW technique [15]. A fractured medial cortex in LCW may lead to progressive movement of the distal tibia into a varus position [19]. In case of the MOW, instability at the MOW site due to disruption of the lateral cortical hinge potentially results in displacement of the osteotomy and may contribute to recurrent varus deformity [20]. Newer angular stable plate systems with locking screws seem to avoid this problem. Loss of correction may lead to a suboptimal result [11,21,22]. Still, HTO is considered a very successful surgical procedure with low complication rates. For instance, non-union in HTO is very rare, especially in LCW, and delayed union is seen in about 3-4% [23,24].

A Cochrane review showed no evidence as to whether LCW or MOW is more effective in the treatment of symptomatic medial knee OA. A relatively new HTO technique, the combined valgus-producing high tibial osteotomy (CWO), claims to include the advantages of both the LCW and MOW techniques for HTO. This HTO modification avoids metaphyseal tibial bone loss, decreasing transposition of the tibial condyle and shortening of the patellar tendon after osteotomy, even in cases of great correction [14]. Both the LCW and CWO techniques have been commonly used for HTO at the Orthopedics Department of Martini Hospital for years now. The clinical results of the CWO technique are very promising. So far there is little scientific evidence on its effectiveness though. Hence the aim of this prospective randomized trial (RCT) is to compare LCW with CWO in patients eligible for HTO.

## Abbreviations

OA: Osteoarthritis; HTO: High tibial osteotomy; LCW: Lateral closing wedge HTO; MOW: Medial opening wedge HTO; CWO: Combined wedge osteotomy; RCT: Randomized controlled trial; WLR: Whole-leg radiograph; HKA: Hip-knee-ankle angle; TKR: Total knee replacement.
